**Session 1: Introduction to Pre-DICTED Program and Nutrition Workshop 1: Learn to Eat Healthy today**	
Instil commitment to the Pre-DICTED Program by understanding the importance of lifestyle intervention in diabetes prevention. Highlight the two study goals: 5% weight loss and 150 minutes of weekly physical activity. Understand what diabetes is and how to adopt healthy eating habits as well as how food can affect blood sugars. Introduce tips to manage blood sugar levels through dietary modifications. Learn about food labels and Healthier Choice Symbols. Understand food composition and types of carbohydrates.	
**Session 2: Nutrition Workshop 2: Taking Charge of One’s Meals**	
Explore sugar content in common foods and drinks. Encourage participants to minimize intake of food and drinks with added sugars. Learn about “good fats” and “bad fats”. Learn about the beneficial effects of fiber and sources of fiber. Educate on healthier cooking methods. Introduce tips to self-monitor food intake and build healthy eating habits. Develop a plan for carrying out the changes.	
**Sessions 3 to 11: Exercise sessions: Living a Healthy Life Through Physical Activities**	
Introduce basic principles of physical activity and work towards a minimum of 150 minutes of weekly physical activity over the next 6 weeks. Encourage attendance at group supervised exercise sessions. Experience a range of physical activities, including aerobic and stretching exercises, that is fun and inclusive to invoke continuity in exercising. Learn how to measure heart rate and perceived level of exertion as a way of determining the appropriate levels of activity. Begin self-monitoring of physical activity.	
**Session 12: Goal setting**	
Develop an action plan for physical activity and healthy eating. Learn to find the time to be physically active each day by including short bouts (10–15 min) of activities and record the duration of physical activity. Record food intake and plan for healthy and balanced meals. Start self-monitoring of body weight with intention to achieve study goal of 5% weight loss.	

##### Maintenance phase (months 4 to 36)

During this phase, the participants receive monthly mobile phone text messages on health tips as well as 6-monthly telephone calls from study coordinators to discuss the progress of their lifestyle modifications.

#### Stepwise addition of metformin

The stepwise addition of metformin is done at 6, 12, 18, 24, or 30 months for intervention arm participants who, despite 6 months of lifestyle interventions, are considered to be at the highest risk of conversion to diabetes, defined as having IFG + HbA1c ≥ 6.0% or IFG + IGT. Metformin is prescribed at a starting dose of 250 mg twice daily followed by up-titration to 500 mg twice daily after 3 months if the participants do not experience any side effects. If participants experience side-effects with metformin, the dose is adjusted by the study investigators accordingly. Once added, metformin is prescribed for the remaining study period, ranging from 6 (i.e., added at month 30) to 30 months (i.e., added at month 6). Metformin is discontinued at the end of the study or at the point of diabetes conversion.

#### Financial incentives

In the Pre-DICTED program, participants randomized to the intervention arm are given financial incentives for program adherence and weight loss achievement. Intervention arm participants are given a financial incentive of S$10 (sports vouchers) for attending each group session during the core intervention phase (maximum amount for 12 sessions = S$120). They are also eligible for financial incentives (cash) if they meet the weight loss target (≥ 5% of baseline weight) at any of the study visits at 3, 6, 12, 18, 24, 30 and 36 months. They can receive multiple payments if they maintain the 5% weight loss for subsequent study visits. Payment is interrupted if they fail to maintain the 5% weight loss but they are eligible for payment if they re-meet the target in subsequent visits. The weight loss target is logged-in following the baseline visit and conveyed to the participants. Each participant who meets the weight loss target is given the option of choosing either guaranteed payment or lucky draw payment (1 in 10 chance) according to the schedule in Table 2. The maximum (guaranteed) payment for any participant will be $40 + $50 + $60 + $70 + $80 + $90 + $100 = $490.

**Table 2 Tab2:** Schedule of guaranteed payment and lucky draw payment for meeting weight loss target (≥ 5% of baseline weight) for intervention arm participants

Month	Guaranteed payments	Lucky draw payments (1 in 10 chance)
3	S$40	S$400
6	S$50	S$500
12	S$60	S$600
18	S$70	S$700
24	S$80	S$800
30	S$90	S$900
36	S$100	S$1,000

### Control group

The current standard of care for pre-diabetes includes referral and follow-up by the participant’s own primary care physician (PCP). The PCPs are instructed to provide individual counseling to the participants on the following topics:
Education on pre-diabetesImportance of lifestyle modifications to prevent progression to diabetes

Participants in the control group follow the same study visits and assessments as those in the intervention group (Table 3). Apart from study visits, participants in the control group will not have additional contact with study coordinators.

**Table 3 Tab3:** Schedule of study assessments for all participants

Study phase	Screening phase	Follow-up phase							
Visit	Screening								End of study
Scheduled timeline in months (M) (from the date of baseline assessment)	Within -1 M	0 M	3 M	6 M	12 M	18 M	24 M	30 M	36 M
Participant referral	•								
Informed consent	•								
Inclusion/exclusion criteria		•							
Medical history		•							
Demographics		•							
Randomization		•							
***Physical examinations***									
Weight, height, waist circumference		•	•	•	•	•	•	•	•
Heart rate		•	•	•	•	•	•	•	•
Systolic and diastolic blood pressure		•	•	•	•	•	•	•	•
***Laboratory assessments***									
Cholesterol level: Total cholesterol, HDL-c, LDL-c, triglycerides		•		•	•	•	•	•	•
HbA1c		•		•	•	•	•	•	•
Fasting plasma glucose		•		•	•	•	•	•	•
2-hour plasma glucose		•			•		•		•
75 g OGTT		•^a^			•		•		•
***Retinal photography***									
Vision media opacity, diabetic retinopathy, diabetic maculopathy		•			•		•		•
***Questionnaires***									
Food Frequency Questionnaire		•		•	•				
Health status (EQ-5D-5L)		•		•	•	•	•	•	•
Physical activity (IPAQ)		•		•	•	•	•	•	•
Work impairment (WPAI:GH)		•		•	•	•	•	•	•

^a^Participants referred based on FPG alone will need to undergo OGTT at baseline

*HDL-c* high-density lipoprotein-cholesterol, *LDL-c* low-density lipoprotein-cholesterol

### Retention of participants

Appointment reminders have improved attendance in chronic disease follow-up [28], and monetary incentives have demonstrated effectiveness in improving retention in trials [29, 30]. To minimize dropouts, all participants, both controls and those in the intervention group, are given text messaging reminders and telephone call reminders by the study coordinators prior to every study visit. All participants are also asked to make an upfront payment of S$20 as a form of deposit contract. This amount is forfeited if the participant drops out of the project before the end of 3 years or project closeout. The entire amount is quadrupled (i.e., S$80) and returned to the participant if he/she completes the last study visit at the end of the third year. In addition, 6-monthly lucky draws of S$50 sports vouchers (20 vouchers per draw) are conducted for all participants who complete their follow-up visits. They are eligible for multiple draws during the study period.

### Endpoints

#### Primary endpoint

The primary endpoint is the proportion of participants who develop diabetes within 3 years from the baseline visit. Diabetes is diagnosed on the basis of a single FPG of ≥ 7.0 mmol/L or a 2-h plasma glucose of ≥11.1 mmol/L, in accordance with the criteria of the American Diabetes Association [31]. An FPG test is conducted every 6 months, and an OGTT is conducted annually.

#### Secondary endpoints

Secondary endpoints include the change from baseline to end-of-study (3 years) in the following outcome measures:
HbA1cFPGTwo-hour plasma glucoseBody weightBMIWaist circumferenceDietary intake (assessed by the Food Frequency Questionnaire (FFQ) [32])MET-minutes per week (assessed by the International Physical Activity Questionnaire (IPAQ) [33])Health status scores (assessed by the EQ-5D-5L [34])Work productivity loss and activity impairment (assessed by the Work Productivity and Activity Impairment Questionnaire: General Health V2.0 (WPAI:GH) [35])

Secondary endpoints also include the proportion of participants who have engaged in the targeted level of physical activity (≥ 150 min/week of walking, moderate activity, or vigorous activity as defined by the IPAQ [33]).

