**Methods:**

This is an open-label, 1:1 randomized controlled trial which aims to recruit 846 adult individuals with isolated impaired fasting glucose (IFG), isolated impaired glucose tolerance (IGT), or both IFG and IGT from Singapore. Intervention arm participants attend 12 group-based sessions (2 nutrition workshops, 9 exercise sessions, and a goal-setting workshop) delivered at community sites (weeks 1 to 6), receive weekly physical activity and nutrition recommendations delivered by printed worksheets (weeks 7 to 12), and receive monthly health tips delivered by text messages (months 4 to 36). From month 6 onwards, intervention arm participants who remain at the highest risk of conversion to diabetes are prescribed metformin. Intervention arm participants are also eligible for a payment/rewards program with incentives tied to attendance at the group sessions and achievement of the weight loss target (5% of baseline weight). All participants are assessed at baseline, month 3, month 6, and every 6 months subsequently till month 36. The primary endpoint is the proportion of participants with diabetes at 3 years. Secondary endpoints include the mean change from baseline at 3 years in fasting plasma glucose, 2-hour plasma glucose, HbA1c, body weight, body mass index, physical activity, and dietary intake.

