### Assessments and visit schedule

Baseline measurements (questionnaire completion, physiological and anthropometric measurement, retinal photography) are taken for all participants. Participants who are referred based on FPG alone also undergo a 75-g OGTT at the baseline visit. Follow-up visits are conducted at month 3 and every 6 months from the date of randomization (6, 12, 18, 24, 30, and 36 months). The acceptable tolerance in the 6-monthly visits is +/− 1.5 months. All assessments are performed by trained study coordinators following standard operational procedures and unaware of participants’ study group allocation. Study visits and assessments are summarized in Table 3. The assessments are described below.

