Secondary outcomes (engagement in ≥150 minutes of physical activity per week; change from baseline in the following outcomes: HbA1c, FPG, 2-hour plasma glucose, body weight, BMI, waist circumference, health status scores, MET-minutes per week and activity impairment score) will be analyzed using generalized linear models. Subgroup analyses will also be performed, with participants stratified by baseline age (< 50 years, ≥ 50 years), sex, pre-diabetes type (isolated IFG, isolated IGT, IFG + IGT), HbA1c (< 5.7%, 5.7–6.4%, ≥ 6.5%), family history of diabetes, BMI (23.0 to 27.4 kg/m^2^, ≥ 27.5 kg/m^2^), physical activity level (< 150 min/week, ≥ 150 min/week of physical activity), ethnicity (Chinese, Malay, Indian, others), and average monthly income (< S$5000, ≥ S$5000). Baseline characteristics, intervention adherence, and adverse events will be summarized using descriptive statistics.

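### Dietary intake is declared as a 3-year change, but the schedule stops the Food Frequency Questionnaire at month 12, so this secondary endpoint has no scheduled data at its declared time

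*Protocol article*

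**What the plan says.** Two places in the protocol article fix the time point. The Secondary endpoints section opens "Secondary endpoints include the change from baseline to end-of-study (3 years) in the following outcome measures", and dietary intake is one of the listed measures, with the FFQ as its only instrument. The Methods part of the abstract states "Secondary endpoints include the mean change from baseline at 3 years in fasting plasma glucose, 2-hour plasma glucose, HbA1c, body weight, body mass index", and the list closes with "body mass index, physical activity, and dietary intake".

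The schedule is in Table 3, under Control group, and applies to both arms. Its visit columns read "Within -1 M 0 M 3 M 6 M 12 M 18 M 24 M 30 M 36 M". The row "Food Frequency Questionnaire" is marked at 0, 6 and 12 months, with nothing at 18, 24, 30 or 36. The rows for the EQ-5D-5L, the IPAQ and the WPAI:GH are marked at 0, 6, 12, 18, 24, 30 and 36 months.

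The text adds no other timing. Assessments and visit schedule says "Study visits and assessments are summarized in Table 3". The Dietary intake paragraph describes the 163-item instrument and its outputs but names no visit.

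The Statistical analyses section itemises the secondary outcomes to be modelled as changes from baseline. That list ends "health status scores, MET-minutes per week and activity impairment score". Neither dietary intake nor work productivity loss is in it.

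**The concern.** A change from baseline to 3 years needs a measurement at baseline and one at month 36. The schedule provides only the first. Followed as written, the team would have to drop the declared endpoint or report the change at month 6 or month 12 under a definition that the article does not contain. If that choice is made and recorded only after results by arm are known, a reader cannot tell whether it was made independently of them.

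The content of the claim also matters. Diet is a direct target of the intervention, with two nutrition workshops in the core phase. The maintenance phase runs from month 4 to month 36. A month-12 FFQ covers only the early part of it and cannot show whether a dietary change lasts to 3 years.

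**Working it through.** No sample size, power or alpha figure underlies this point. The check is a reading of Table 3 against the endpoint definitions.

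**1. Map the rows to the nine visit columns** (screening, then months 0, 3, 6, 12, 18, 24, 30, 36).

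| Table 3 row | Cells | Marked months |
|---|---|---|
| FFQ | 9 | 0, 6, 12 |
| EQ-5D-5L | 9 | 0, 6, 12, 18, 24, 30, 36 |
| Fasting plasma glucose | 9 | 0, 6, 12, 18, 24, 30, 36 |
| 2-hour plasma glucose | 9 | 0, 12, 24, 36 |

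**2. Rule out a text-extraction fault.** The FFQ row keeps all nine cells, including the empty ones at the end. The 2-hour glucose row gives annual testing and the fasting glucose row gives 6-monthly testing after baseline, both as stated under Primary endpoint. The columns are therefore aligned and the empty FFQ cells are genuine.

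**3. Compare what is needed with what is scheduled.** Needed: months 0 and 36. Scheduled: months 0, 6 and 12. Gap from the last FFQ to the endpoint: 36 − 12 = 24 months.

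**4. Check whether the visit window helps.** The tolerance is ±1.5 months. The latest month-12 visit is at 12 + 1.5 = 13.5 months and the earliest month-36 visit is at 36 − 1.5 = 34.5 months. The difference is still 21 months. The longest change that the schedule supports is baseline to month 12.

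**5. Compare the endpoint list with the analysis list.** Counting work productivity loss and activity impairment separately, the Secondary endpoints section names 11 change measures: HbA1c, FPG, 2-hour glucose, weight, BMI, waist circumference, dietary intake, MET-minutes, health status, work productivity loss and activity impairment. The Statistical analyses section names 9 of them. The two missing are dietary intake and work productivity loss. The second has no timing problem, because the WPAI:GH is scheduled through month 36.

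**6. Ask whether a month-36 FFQ is still possible.** Recruitment began on 15 November 2017, so the first participants reached month 36 around November 2020. The article reports an interim analysis performed in February 2021 and expects recruitment to end in May 2021, about 42 months after it began. The accrual curve is not given. Assuming uniform accrual over those 42 months, the share of planned participants already past month 36 would be:

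- in February 2021 (39 months after the start): (39 − 36)/42 = 3/42 ≈ 7%;
- in May 2021 (42 months after the start): (42 − 36)/42 = 6/42 ≈ 14%.

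Front-loaded accrual would raise these figures. On the uniform assumption, most participants could still have been given an FFQ at month 36 at that time.

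**The case against.** The best defence concerns weight. Dietary intake is one of about ten secondary change measures. The primary endpoint, the sample size, the primary analysis and the safety monitoring do not depend on it. That stands, and it limits the severity.

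A second defence is that a journal article condenses the full protocol, and that the handling of a multi-part FFQ (food groups, energy, macronutrients, fibre, micronutrients) is commonly left to an analysis plan. This has some force for how diet is modelled, so the analysis-list omission is the lesser part of the point. It does not answer the timing conflict, where the article states both the endpoint time and the schedule and the two disagree.

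Several stronger readings are tempting, and the documents do not support them:

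- A reader might infer that the 3-year dietary endpoint is already beyond rescue because the earliest participants have passed month 36. That is true only of the earliest. With recruitment open until about May 2021 and no accrual curve given, an FFQ added at month 36 could still serve those in follow-up.
- A reader might infer that a time point will be picked to suit the results. The article shows an opening for this, limited to two post-baseline visits, but no sign that it has happened or will.
- A reader might treat work productivity loss as a second endpoint without data. It is scheduled at month 36 and is only absent from the analysis list.
- A reader might want the registry entry changed as well. The record is not shown, so nothing can be said about its wording.

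**Conclusion.** The point holds as an internal inconsistency that should be fixed. The abstract and the endpoint list promise a 3-year change in dietary intake; Table 3 schedules no FFQ after month 12. As written, no participant has a scheduled FFQ at the declared time. The effect is confined to one secondary endpoint.

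The conclusion assumes that Table 3 is the operative schedule. If the table is misprinted and the FFQ is collected at month 36, the data exist and the table is the error; the article still needs correcting. The mismatch between the endpoint list and the analysis list is real but secondary.

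**What to change.** Before the secondary outcomes are analysed, make the abstract, the Secondary endpoints section and Table 3 agree.

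- **If Table 3 is right:** redefine the dietary endpoint as change from baseline to month 12 in the abstract and the endpoint list. This is a wording amendment. The cost is that the dietary claim becomes a 1-year claim and says nothing about persistence to 3 years.
- **If the FFQ is in fact collected at month 36, or is added there for participants still in follow-up:** correct Table 3 instead, keep the 3-year definition, and state that participants already past month 36 may lack the measurement. If it is newly added, the cost is one more 163-item questionnaire per participant and an incomplete endpoint. Gaps due only to the date of the amendment would follow enrolment date, so they should not in themselves favour either arm, but the number analysed would be smaller and should be reported.

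In either case, align the list in Statistical analyses with the endpoint list by adding dietary intake at the chosen time point and work productivity loss at month 36. This adds two outcomes to the planned models and no new data collection beyond any FFQ decided on above. Date and record the decision so that it can be seen to precede the analysis.

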### Assessments and visit schedule

Baseline measurements (questionnaire completion, physiological and anthropometric measurement, retinal photography) are taken for all participants. Participants who are referred based on FPG alone also undergo a 75-g OGTT at the baseline visit. Follow-up visits are conducted at month 3 and every 6 months from the date of randomization (6, 12, 18, 24, 30, and 36 months). The acceptable tolerance in the 6-monthly visits is +/− 1.5 months. All assessments are performed by trained study coordinators following standard operational procedures and unaware of participants’ study group allocation. Study visits and assessments are summarized in Table 3. The assessments are described below.

#### Anthropometry

Measurement of body weight, height, waist circumference, and blood pressure is performed at all visits. Height and body weight are measured in light indoor clothing and without shoes, using a portable stadiometer (Model Seca 213, Gmbh & Co.KG, Hamburg, Germany) and a digital weight scale (Model Seca 803, Gmbh & Co.KG, Hamburg, Germany) respectively. Waist circumference is measured at the midpoint between the lower margin of the last palpable rib and the top of the iliac crest, using a stretch-resistant tape. Two waist circumference measurements are made, and the mean value is used. If the two measurements differ by more than 1 cm, both measurements are repeated. Blood pressure and heart rate are measured with the participant in a sitting position after at least 5 min of rest, using a digital blood pressure monitor (Model HEM-7322, Omron Healthcare Co. Ltd, Kyoto, Japan). The first heart rate measurement is used, while the measurement is repeated for blood pressure. If the two measurements differ by more than 5 mmHg for diastolic blood pressure or 10 mmHg for systolic blood pressure, a third measurement is made. The mean value of the closest two blood pressure measurements is used.

#### Physiological measures

For HbA1c, FPG, 2-h plasma glucose in OGTT and lipids profile, participants are instructed to fast overnight for at least 10 h. Blood samples are collected from participants using standard phlebotomy procedures. Plasma glucose is assessed by photometry (ADVIA Chemistry, Siemens, Germany), and HbA1c is assessed by high-performance liquid chromatography (D100 System, Bio-Rad, USA). Serum total cholesterol, HDL-cholesterol and triglycerides are measured by means of enzymatic techniques (ADVIA Chemistry, Siemens, Germany). Additional blood specimens are collected at baseline and month 36. These specimens are stored for future general research beyond the completion of the study.

#### Retinal photography

Retinal photographs are captured using a handheld non-mydriatic fundus camera (Visuscout 100, Zeiss, Germany) by trained technicians. Two fundus images are captured from each eye. The images are subsequently graded for the presence or absence of diabetic retinopathy by trained non-physician graders at a central ocular grading center [36].

#### Questionnaires

##### Dietary intake

Dietary intake is assessed using a locally-validated 163-item semi-quantitative FFQ [32]. The questionnaire consists of a list of 163 food/beverage items, and participants are asked how often they consumed one serving of each item. Data on the responses will be combined with local data on the nutrient content of each FFQ item to calculate the daily intake of major food groups (e.g., vegetables), energy, macronutrients as a percentage of energy intake, and fiber and micronutrient intakes as amount per 1000 kcal.

